#### External validation

We will externally validate (as far as possible) the models in patients admitted with a diagnosis of early-onset pre-eclampsia in two prospective datasets: The Pre-eclampsia Eclampsia TRial Amsterdam (PETRA), Netherlands, and Pre-eclampsia Integrated Estimate of RiSk for mothers (PIERS), Canada. We will compare the predicted number of events from our model with the observed events in the external datasets to assess calibration for the logistic model and compare the predicted with the observed survival function for the survival model (as described above). We will also calculate the *C*-statistic curve to assess discriminatory ability.

The models we develop (which use data from women diagnosed with pre-eclampsia) will also be tested in women defined with suspected pre-eclampsia (urine dipstick 1+ on admission but normal 24-h proteinuria, <300 mg/24 h and normal PCR <30 mg/mmol). Such women will have been identified from our recruitment process, and by checking the calibration and discrimination of our models for such patients, we can examine the potential generalisability to a broader set of women.

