### Inclusion criteria

Women aged 16 years or over and a diagnosis of new-onset or superimposed pre-eclampsia at gestational age between 20 + 0 and 33 + 6 weeks will be considered for inclusion in the study. Women with a diagnosis of HELLP (haemolysis, elevated liver enzymes, low platelets) syndrome and those with one episode of eclamptic seizures without hypertension or proteinuria will be considered for inclusion. All women will be required to provide written informed consent and must be capable of understanding the information provided. The definitions for the diagnosis of pre-eclampsia are provided in Table 1.

**Table 1 Tab1:** Definition of the inclusion criteria for recruitment into the PREP study

Condition	Definition
New-onset pre-eclampsia	New-onset hypertension (systolic BP ≥140 mmHg or diastolic BP ≥90 mmHg on 2 occasions 4–6 h apart in women) after 20 weeks of pregnancy and new-onset proteinuria (≥2+ in urine dipstick or PCR of greater than 30 mg/mmol or 300 mg of protein excretion in 24 h) [37]
Suspected pre-eclampsia	New-onset hypertension (systolic BP ≥140 mmHg or diastolic BP ≥90 mmHg on 2 occasions 4–6 h apart in women) after 20 weeks of pregnancy and 1+ proteinuria on urine dipstick
Superimposed pre-eclampsia	
- In women with chronic hypertension and no proteinuria before 20 weeks’ gestation	New-onset proteinuria (as defined previously)
- In women with significant proteinuria before 20 weeks’ gestation	Elevated serum alanine aminotransferase concentration (>70 U/L) or worsening hypertension (either 2 diastolic BP of at least 110 mmHg 4 h apart or 1 diastolic measurement of at least 110 mmHg if the woman had been treated with an anti-hypertensive drug), plus one of the following: increasing proteinuria, persistent severe headaches or epigastric pain
HELLP syndrome	Haemolysis, elevated liver enzymes, and low platelets syndrome: presence of haemolysis based on examination of the peripheral smear, elevated indirect bilirubin levels or low serum haptoglobin levels in association with significant elevation in liver enzymes and a platelet count below 100,000/mm^3^ after ruling out other causes of haemolysis and thrombocytopenia
1 episode of eclamptic seizures without hypertension or proteinuria	Other neurological conditions of seizures have been excluded

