### Exclusion criteria

Women will be excluded if any of the outcomes (including recurrent eclamptic seizures) occurs prior to testing or if informed consent could not be obtained on time or if the mother does not have a good understanding of spoken and written English and a translator is unavailable.

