### Statistical analysis

We will develop two prediction models: a survival model for adverse maternal outcomes at various time points from diagnosis up to 34 weeks of gestation, including by 48 h after admission, and a logistic model for adverse maternal outcomes by discharge. These will both be developed using a general methodological and statistical framework as outlined below.

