#### Model development, apparent performance assessment and internal validation

The predictors of adverse maternal outcomes will be identified to develop and externally validate a simple, interpretable and clinically applicable prediction model with face validity. We will use a transparent process that implements appropriate statistical methods and adheres to current methodological recommendations.

A backwards selection procedure will be used to decide which of the candidate predictor variables should be included in the final prediction model (with *p* < 0.15 taken conservatively to warrant inclusion). Continuous variables will be kept as continuous in the model (rather than dichotomising), to avoid a loss of power [27, 28]. Non-linear trends will also be considered using the multivariable fractional polynomial procedure [29, 30], which uses multivariable models to eliminate weaker predictors and identify transformations of continuous predictors that best predict outcome. Large amounts of missing variable data are not expected, but some will inevitably occur, with not all patients providing all variables of interest. Multiple imputation will be used to impute, with 5 imputations, under a missing at random assumption, missing values so as to avoid excluding patients from the analysis [27].

For survival analysis, failure event is defined as an adverse outcome or delivery occurring before 34 weeks of gestation. We will use a flexible parametric survival model via the Royston-Parmar approach [31–33], with the cumulative baseline hazard scale modelled using restricted cubic splines. The number of knots will be chosen by visual inspection. For the binary adverse maternal outcome by discharge, a logistic regression-modelling framework will be undertaken with the logit probability of an adverse outcome being the response variable.

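### The suspected pre-eclampsia test set is selected partly on a 24-h urine result that normally arrives inside the 48-h prediction window, so early events are likely to be under-represented

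*Protocol article*

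**What the plan says.** Four parts of the protocol article bear on this.

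- **External validation.** The models, developed in women with diagnosed pre-eclampsia, are also tested in a suspected group defined by "urine dipstick 1+ on admission but normal 24-h proteinuria, <300 mg/24 h and normal PCR <30 mg/mmol". The stated purpose is that "by checking the calibration and discrimination of our models for such patients, we can examine the potential generalisability to a broader set of women".
- **Statistical analysis.** The survival model predicts "adverse maternal outcomes at various time points from diagnosis up to 34 weeks of gestation, including by 48 h after admission".
- **Model development, apparent performance assessment and internal validation.** For the survival model, "failure event is defined as an adverse outcome or delivery occurring before 34 weeks of gestation".
- **Inclusion criteria, Table 1.** Suspected pre-eclampsia at recruitment means new hypertension "after 20 weeks of pregnancy and 1+ proteinuria on urine dipstick". No 24-h collection or PCR result is required.

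The Exclusion criteria add that "Women will be excluded if any of the outcomes (including recurrent eclamptic seizures) occurs prior to testing", without saying which test is meant. The article gives no separate time origin, landmark or delayed entry for the suspected group, and does not say when the urine collection starts.

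**The concern.** A test set for a prediction model should be fixed by what is known when the prediction is made. Here the dipstick is an admission finding, but the 24-h protein result normally becomes known later, within a horizon only twice as long as the collection itself. A woman with a 1+ dipstick and a normal PCR who delivers on the first day may never have a 24-h result. She met Table 1 for suspected pre-eclampsia at recruitment, yet she would satisfy neither the definition of the test set nor, on those results, the definition of confirmed disease.

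The failure event makes this matter, because delivery before 34 weeks counts as failure and would tend to cut an antenatal collection short. The selection is also asymmetric. Table 1 lets women enter as confirmed cases on a dipstick of 2+ or a raised PCR, with no 24-h wait, so the development group can contribute first-day events freely.

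What is at stake is how the calibration check is read. An observed survival curve that is too flat in the first day would look like over-prediction at 48 h in a lower-risk group. It could suggest poor transport or prompt a recalibration that is not needed.

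**Working it through.** **The plan's own figure.** The article gives no event rate, sample size or timing for the suspected group, so there is no figure to reproduce. The 20% in Sample size considerations is the risk by discharge, before delivery under 34 weeks joined the composite. It is not a 48-h risk. The risks below are assumptions.

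**Inputs**
- Horizon: 48 h from admission (Statistical analysis).
- Collection length: 24 h (External validation).
- *p*: true 48-h risk in women who are suspected cases at admission (assumed).
- *f*: share of the 48-h cumulative hazard falling in the first 24 h (assumed; 0.5 is a constant hazard).
- *q*: fraction of women with a first-24-h event who still complete the collection and stay in the set (assumed).

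**Step 1: how much of the window is exposed.** If the collection starts at admission, it covers 24/48 = 50% of the window. This is an upper limit: a collection already running at admission covers less.

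**Step 2: no early-event woman retained (*q* = 0).** Observed risk = 1 − (1 − *p*)^(1 − *f*). With *f* = 0.5 this is 1 − √(1 − *p*).

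| True *p* | Observed | Observed/true |
|---|---|---|
| 10% | 5.1% | 0.51 |
| 20% | 10.6% | 0.53 |
| 30% | 16.3% | 0.54 |

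**Step 3: timing of the hazard, *p* = 20%, *q* = 0.**
- *f* = 0.3: 1 − 0.8^0.7 = 14.5% (ratio 0.72).
- *f* = 0.7: 1 − 0.8^0.3 = 6.5% (ratio 0.32).

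**Step 4: some early-event women retained, *f* = 0.5.** Let *a* = 1 − √(1 − *p*), the risk in each 24-h half. Then

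observed = [*aq* + (1 − *a*)*a*] / [1 − *a*(1 − *q*)].

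For *p* = 20%, *a* = 0.1056. With *q* = 0.5 the numerator is 0.0528 + 0.0944 = 0.1472 and the denominator is 1 − 0.0528 = 0.9472, giving 15.5%.

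| *q* | Observed (true 20%) | Observed/true |
|---|---|---|
| 0 | 10.6% | 0.53 |
| 0.25 | 13.1% | 0.66 |
| 0.5 | 15.5% | 0.78 |
| 1 | 20.0% | 1.00 |

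**Step 5: longer horizons.** One exposed day is 50% of a 48-h window, but 24/168 = 14% of a one-week window, and less beyond that. The effect is therefore concentrated at the 48-h prediction.

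**The case against.** The strongest reply is that the article never requires these women to be event-free until the collection ends. Several components in Table 3, such as transfusion, raised creatinine or pulmonary oedema, need not stop a urine collection. Recruitment includes antenatal clinics and day assessment units (Study design and conduct), so a collection may begin before admission. The clock for women who never meet the diagnosis is not explicit: the text speaks both of diagnosis and of admission. The exclusion for outcomes before testing cuts either way. If follow-up starts at testing, the protected time disappears; if it starts at admission and testing includes the urine collection, early events are removed outright. The joint requirement for a normal 24-h result and a normal PCR may be loose wording for whichever test was done. Finally, this is an added check, separate from internal validation and from the PETRA and PIERS cohorts.

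Much of this stands, and it rules out stronger readings. A reader might infer that the women are event-free for half the window by construction, that the model will appear to over-predict about two-fold, that discrimination is driven by the women lost, or that the generalisability conclusion would be wrong. The documents support none of these. The two-fold figure needs collection from admission, constant hazard and no early-event woman retained, all together. Harrell's C uses the whole follow-up.

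The direction of the bias is not removed. Read as written, both urine results are required, which is also the logical complement of Table 1's either/or rule for confirmed proteinuria. Admission is the only stated origin for the 48-h horizon. For a collection that runs on after admission, the bias vanishes only if every woman with an early event completes it, or if the clock starts at the result.

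**Conclusion.** The point holds in a limited form. As written, membership of the suspected set depends on information that normally arises after the admission time origin of the 48-h prediction. Women with an event or delivery during the collection are likely to be under-represented, and up to half of the 48-h window may be partly protected from events. The expected effect is a lower observed early risk and apparent over-prediction by the survival model at 48 h.

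The size cannot be determined from the article. With an assumed true 48-h risk of 20%, constant hazard and collection from admission, the observed risk lies anywhere from 10.6% to 20%, depending on how many women with early events complete the collection. A hazard concentrated in the first day would lower the bottom of that range; a collection begun before admission would shrink the shortfall. The by-discharge model and longer horizons are much less exposed. This is more than detail left to a fuller document, because the membership rule that is printed is itself the source of the selection. It deserves correction, in proportion to a supporting analysis.

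**What to change.** For this validation analysis, choose one of two rules and state it.

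1. **Membership from time-zero results.** Define the set by the 1+ dipstick and, where available, a spot PCR below 30 mg/mmol. Reconcile this with the suspected definition in Table 1, and keep each woman in the set whatever later tests show. Cost: some women whose 24-h result would later be abnormal stay in the set.
2. **Landmark at the 24-h result.** If the 24-h criterion is kept, start the 48-h clock and take predictor values when that result is available. Limit the conclusion to women event-free at that point. Cost: the conclusion covers a narrower group and no longer speaks to risk from admission.

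Under either rule, say which test the exclusion for prior outcomes refers to. The first option is a sentence or two and needs no new data. The second also needs the time of the result and predictor values at that time.

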## Discussion

Pre-eclampsia and its complications are still considered to be one of the leading causes of maternal and fetal morbidity and mortality; the condition utilises a large proportion of NHS resources. Accurate prediction and early management can significantly improve these outcomes. However, clinicians and policymakers currently do not have the evidence on which they can base their recommendations.

Timely prediction of complications in women with early-onset pre-eclampsia involves the use of a combination of maternal characteristics, symptoms, physical signs and investigations [21]. These ‘tests’ are to some extent haphazardly performed in all units, due to the absence of a structured approach. The most important determinant of perinatal outcome is gestational age, with more than half the chance of intact fetal survival when this is more than 27 weeks and the birth weight is more than 600 g [34].

A recent Cochrane review [10] has shown that expectant management reduced risk of fetal and neonatal complications without increase in maternal complications. Clinicians are reluctant to promote expectant management due to uncertainties around the scale of maternal risk. One of the main reasons for this lack of confidence in applying risk scores in practice is the absence of sufficient evidence to show the reproducibility and transportability of the model in a different population [11]. A good performing prediction model is one that is accurate, validated in populations and datasets external to those used to develop the model, widely applicable in practice, and acceptable to patients and ultimately improves clinical outcomes by helping clinicians and patients make more informed decisions. With very small numbers of cases and events per variable, early-onset pre-eclampsia contributed little to current published models [8, 35, 36].

It is currently difficult to identify those mothers with early-onset pre-eclampsia who are at increased risk of developing complications, and this risk cannot be graded. There is a need for a prognostic model to include the predictive role of more than one test results on the outcome with individualised risk assessment. Provision of individualised risk estimates for adverse maternal outcomes through the PREP study will help clinicians make suitable decisions after discussion with the parents.

Ideally, to develop a prediction model, we would like to observe outcomes in a cohort of women who receive no clinical management at all to be able to predict the likelihood of an adverse outcome independent of clinical management. Clearly, this is unethical and all women who present with pre-eclampsia receive clinical management, but such clinical decisions also affect maternal outcomes. Thus, in the development of our prediction model, we must recognise the importance of accounting for current clinical management; however, this is currently an under-researched methodological issue. By including effective treatment measures such as use of anti-hypertensives and magnesium sulphate predictor variables, and delivery before 34 weeks as a component of the composite outcome, we plan to negate some of the bias arising from treatment paradox in prediction models [23].

There is no obvious single outcome measurement that determines clinical management in early-onset pre-eclampsia. As the risk of more than one outcome needs evaluation simultaneously, we have chosen a composite measure consisting of several complications [37]. The composite outcomes are constructed by including those components whose underlying biology is similar [38].

To show that the PREP prognostic model is valuable, it is not sufficient to show that it successfully predicts outcome in the initial development data even after having it being internally validated. We need evidence that the model performs well for other (external) patients. The resulting geographical and domain validation will enable us to assess the prognostic performance and the generalisability of the model.

Our prediction model plans to use rigorous statistical methods to develop the model and assess accuracy; undertake a formal validation in external datasets (PIERS and PETRA); use unambiguous definitions of predictors and reproducible measurements using methods available in clinical practice; adjust for current clinical management; obtain input from patient focus groups and produce personalised estimates of risk, which enable patients and clinicians to make more informed decisions on management aspects like continuing the pregnancy or delivery of a preterm baby.

## Abbreviations

AUC: Area under the curve (*C*-statistic)
BP: Blood pressure
CEMACH: Confidential Enquiries into Maternal and Child Health
CMACE: Centre for Maternal and Child Enquiries
CTG: Cardiotocography
HELLP: Haemolysis, elevated liver enzymes, low platelets
PCR: Protein-creatinine ratio
PETRA: The Pre-eclampsia Eclampsia TRial Amsterdam
PIERS: Pre-eclampsia Integrated Estimate of RiSk for mothers
PREP: Prediction of Risks in Early onset Pre-eclampsia
RIND: Reversible ischemic neurological deficit
